## Abstract

**Background:**

Interventions targeting single behaviors of preschool-aged children have been mainstream for some time, but integrated interventions targeting all three 24-h movement behaviors (physical activity [PA], sedentary behavior [SB], and sleep hygiene) are less studied. The aims of this study will be to test the feasibility, acceptability, and effectiveness of a parent-focused intervention for preschool-aged children targeting multiple 24-h movement behaviors.

**Methods:**

This three-arm randomized controlled trial will comprise a 12-week intervention and a 12-week follow-up. A total of 150 parent-child dyads will be recruited and randomly allocated to one of three arms: (1) a PA + SB group (dyadic approach), (2) a PA + SB + sleep group (integrated approach), and (3) a wait-list control group. The theory of planned behavior and behavioral change techniques will guide the development of the intervention via workshops, education materials, interactive questionnaires, and reminders. The intervention strategies for the integrated group will be the same as for the dyadic approach except that the intervention will also target sleep hygiene in addition to PA and SB. The primary outcomes will be preschoolers' 24-h movement behaviors (e.g., activity sleep index, compositional data of PA, SB, screen time, and sleep duration). The secondary outcomes will be preschoolers' sleep quality, weight status, cognitive function, and parents' movement behaviors. The feasibility and acceptability of the intervention will also be evaluated.

**Discussion:**

The proposed study will be a theory-based, parent-focused intervention designed to improve all three 24-h movement behaviors among preschoolers. The trial is expected to improve preschoolers' movement behaviors and health outcomes, as well as their parents' movement behaviors. Given the urgent need to promote active lifestyles, our findings will help to determine best practices for movement behavior change among young children.

**Trial Registration:**

The study is prospectively registered at the Chinese Clinical Trial Registry (ChiCTR2200055958).

## Introduction

A healthy lifestyle developed in early childhood is associated with numerous health indicators and tracks into later life (1). Physical activity (PA) (2), sedentary behavior (SB) (3), and sleep (4) in isolation are associated with health in the early years. In addition to their individual effects, the integrated effect of all three movement behaviors in a 24-h day has attracted attention. The World Health Organization (WHO) released 24-h movement guidelines for children under 5 years of age in 2019. Specifically, a healthy day for preschoolers aged between 3 and 4 years should include at least 180 min of PA, of which at least 60 min should be moderate-to-vigorous-intensity PA (MVPA); less than 60 min of sedentary screen time; and 10 to 13 h of good-quality sleep (5). Despite the emerging evidence on 24-h movement behaviors and the promotion of integrated guidelines for the early years, low adherence to the 24-h movement guidelines has been reported in numerous countries (6). In Hong Kong, a recent study found a low compliance rate, with only 2.9% of preschoolers meeting all three 24-h movement guidelines (7). Furthermore, the homeschooling induced by the Coronavirus Disease 2019 (COVID-19) pandemic has led to unfavorable behavior changes. Evidence from several countries indicates that since the outbreak of the pandemic, preschoolers have become more sedentary and had more screen time compared with before the pandemic (8–10). As a result, interventions targeting multiple movement behaviors are warranted and should help to determine best practices for behavior change.

Previous intervention studies have predominantly targeted a single type of movement behavior, particularly PA. Their effectiveness has been summarized in recent systematic reviews (11–13). Interestingly, previous studies have described overflow effects of interventions targeting a single behavior on other non-targeted behaviors. For example, one systematic review reported that interventions aiming to increase PA also reported a decrease in screen time (32 min) for children under 5 years (12). However, given that time is finite and fixed, time spent in PA, SB, and sleep in any 24-h period is not independent and should be viewed as a continuum. In other words, an increase in time spent on one behavior requires an equivalent decrease in time spent on other activities. Studies using statistical models have provided evidence for the effectiveness and flexibility of changing multiple behaviors. Specifically, compositional data analysis found that among adults, similar health outcomes (risk of all-cause mortality) were achieved by different combinations of movement behaviors (14). For example, movement behavior combinations A (light-intensity PA [LPA]: 375 min, MVPA: 3 min, SB: 582 min, sleep: 480 min) and B (LPA: 250 min, MVPA: 55 min, SB: 655 min, sleep: 480 min) during 24 h were associated with a similar risk of all-cause mortality (14). The above evidence suggests that it is necessary to explore whether integrated interventions targeting PA, SB, and sleep simultaneously can generate a larger effect than interventions targeting a single type of behavior. To the best of our knowledge, the only study targeting changes in PA, SB, and sleep simultaneously was conducted in adolescents (15). Compared with the control group, the intervention group had higher PA, lower SB, longer sleep duration, and higher compliance rate to all 24-h movement guidelines after one academic year of intervention (15). However, that study did not evaluate how the 24-h movement behaviors change as a whole, i.e., the composite behavior change. Furthermore, no studies have prospectively targeted changing all 24-h movement behaviors in the early years.

Most behavior change interventions for children under 5 years have been conducted in preschool and childcare settings (11). However, the importance of parental involvement in behavior modifications has been consistently documented (16). A previous systematic review found a greater effect on reducing screen time (−30.6 min/day) for family-based interventions compared to other settings (12). Yoong et al. conducted a study targeting the home routines of preschoolers and found an increase in the sleep of 0.9 h/day after a 3-month intervention (17). Based on the success of family-based interventions targeting single movement behavior, an exploration of the effectiveness of integrated interventions targeting all three 24-h movement behaviors has been recommended (16). Of further note, since the outbreak of the COVID-19 pandemic, preschools have been locked down for a long time and the time that parents spend with their children has significantly increased. A parent-focused intervention to promote 24-h movement behaviors in preschoolers is therefore meaningful and timely.

To fill the research gap and improve understanding of best practices for behavior change in young children, a parent-focused, theory-driven intervention targeting all 24-h movement behaviors for preschool-aged children will be developed. The theory of planned behavior (TPB) will be the theoretical basis for developing this intervention, for several reasons. First, a systematic review found that intention predicted parent-for-child health behaviors, such as reminding and setting limits (18). Second, a study of children in Hong Kong found that parents' perception of the benefits of PA was positively associated with the PA of their children (19). Third, parent-focused TPB-based interventions were effective in improving PA and sleep among preschoolers and children (17, 20). In addition to TPB components, some effective strategies recommended by systematic reviews of interventions in children will be used, such as goal setting, monitoring, and habit development (11, 21, 22). Furthermore, to make the intervention strategies more practical and focused, specific behavior change techniques (BCTs) will be incorporated with the TPB components and strategies (23).

Specifically, the proposed study will (1) test the feasibility and acceptability of a parent-focused intervention targeting multiple 24-h movement behaviors (PA, SB, and sleep hygiene) for preschool-aged children; (2) investigate the effectiveness of a parent-focused intervention to increase PA, reduce SB, and enhance sleep hygiene for preschool-aged children; and (3) examine whether an integrated 24-h movement behavior approach is superior to an intervention targeting daytime behaviors (PA and SB) only. We hypothesize that (1) a parent-focused intervention targeting multiple 24-h movement behaviors for preschool-aged children is feasible and acceptable; (2) both intervention approaches (PA + SB group, PA + SB + sleep group) can effectively change behaviors; and (3) an integrated approach (PA + SB + sleep group) is superior to an intervention targeting daytime behaviors (PA + SB group) only.

## Materials and Methods

### Study Design

The study will be a three-arm randomized controlled trial (RCT) using a 1:1:1 allocation ratio, as shown in Figure 1. The intervention will last for 12 weeks and will be followed by a 12-week post-intervention follow-up. After screening and baseline assessments, parent-child dyads will be randomly allocated to one of three groups: (1) PA + SB group (dyadic approach), (2) PA + SB + sleep group (integrated approach), or (3) wait-list control group. Considering the potential impact of the COVID-19 pandemic, the intervention will be delivered predominantly online (Zoom meetings, online survey using Google Forms). The study will follow the Consolidated Standards of Reporting Trials (CONSORT) Statement for randomized trials (http://www.consort-statement.org/).

**Figure 1 F1:**
[figure not shown]
Flow chart of the study.

### Participants

Kindergartens that have participated in our previous studies will be contacted (7), and more families will be invited using purposive and snowball sampling. The specific inclusion criteria are as follows: (1) families having at least one 3-to-5.9-year-old child; (2) the child is living with parents; and (3) the child does not have any diseases that prevent them from participating in PA or falling asleep. Children who meet all of the 24-hour movement guidelines will be excluded. In a previous study conducted in Hong Kong, less than 3% of preschoolers met all three guidelines (7). Therefore, over-recruitment will be necessary to ensure an adequate sample size. For screening, children will wear an ActiGraph accelerometer for seven consecutive days to measure their PA, SB, and sleep, and parents will respond to a question regarding their child's screen time. Written consent will be sought from parents. Approval from the Research Ethics Committee, Hong Kong Baptist University has been obtained (Ref. No.: SOSC-SPEH-2021-22-200).

### Sample Size

A recent systematic review and meta-analysis found a small but statistically significant effect size for interventions to increase PA in children under 5 years old (11). Intervention studies aiming to reduce SB and improve sleep hygiene among young children reported small to medium effect sizes (17, 24). Based on the above information, a prior analysis was conducted, which indicates that a minimum sample size of 99 (33 per group) is required to detect a small effect size *f* of 0.15 with a power of 0.90 under the conditions of an alpha level of 0.05, three arms (PA + SB group, PA + SB + sleep group, wait-list control group), and four repeated measures assuming a correlation between repeated measures at 0.50. Considering a potential attrition rate of 20% (25, 26), 119 children are needed. Therefore, using an over-sampling procedure, 150 parent-child dyads will be recruited and screened. The power calculation is conducted using G^*^Power 3.1.9.7.

### Intervention

#### Procedure

Data collection will be performed during a school visit at baseline (T1), 6 weeks (mid-term; T2), 12 weeks (immediately after the intervention; T3), and 24 weeks (follow-up; T4). Accelerometers and a take-home package will be distributed to parents via the children. The package will include (1) an information sheet about the ActiGraph and instructions on how to wear the device during the 7-day period; (2) online questionnaires to be completed by parents (assessing parents' PA, SB, screen time, and sleep, children's screen time and sleep quality, and demographic information); (3) a log sheet for parents to record when the device is removed and the reasons for removal and their child's nap time. After the baseline and mid-term measurements, a brief report will be provided to parents, including the current movement behaviors of their child and the differences from the recommended durations. After the final measurement (T4), a complete report presenting the changes in the child's movement behaviors will be provided to each parent.

#### PA + SB Group (Dyadic Approach)

Following the baseline assessment and group allocation, families in the PA + SB group will receive educational materials by email. The materials will include information on the WHO recommendations for preschoolers and materials targeting increasing PA, decreasing SB, and screen time for children. The following materials will be delivered to families biweekly to guide parents to set goals for their child: (1) an individual report on the child's current level of movement behaviors (PA, SB, sleep) and divergence from the guidelines; (2) introduction to setting goals and planning (e.g., specific, progressive, achievable); (3) a schedule for parents to fill in, including biweekly goals for each movement behavior; (4) examples to improve PA and decrease screen time (e.g., games designed for children, including written descriptions and pictures); (5) potential barriers and strategies; and (6) strategies for developing habits.

Three online workshops delivered as Zoom meetings will be held for parents in the intervention groups in weeks 1, 3, and 6. The workshops will aim to explain strategies that can be adopted by parents based on BCTs and TPB to solve problems and to encourage parents to comply with the intervention. Specifically, the first workshop will be a brief lecture for parents about the 24-h movement guidelines and the association between movement behaviors and health outcomes, as well as a general introduction to the program (e.g., how to set individual goals, how to use the materials). The second and third workshops will focus on discussing and providing strategies to overcome barriers that the parents have experienced during the intervention, as well as strategies to develop habits. Each workshop will be held as a group meeting of approximately 10 parents to ensure manageability and feasibility. Activities such as check-in polls, topic-based Q & A sessions, and breakout rooms for small-group discussions will be designed to facilitate the workshops. Each workshop will last for 30 to 45 min. If any parents do not have time to attend the workshops, a recorded video of the workshop will be sent to them, and a phone call will be made to provide a brief introduction to the workshop, ask whether they have had any challenges, and suggest strategies. Every 2 weeks, the parents will be asked to complete an online questionnaire using Google Forms. The questions will relate to the children's movement behaviors (e.g., average PA, SB, screen time, bedtime, and wakeup time), whether and how they have used the planning materials for each movement behavior, whether they have achieved the goals and schedules for the coming 2 weeks, etc. At the end of each questionnaire, reminders about the materials use will be presented.

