#### Wait-List Control Group

Parents in the wait-list control group will not receive the intervention. They will be given access to the educational materials after the intervention and follow-up.

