### Statistical Methods

Analyses will be performed using SPSS 27.0. The significance level will be set at 0.05. Descriptive statistics will be presented for the children's baseline movement behaviors. Feasibility and acceptability will be presented using percentages. Differences in movement behaviors across three groups at baseline will be assessed using analysis of covariance. The intention-to-treat principle (all participants) and sensitivity analysis (participants with complete data) will be used to compare primary outcomes between groups. Generalized estimating equations will be applied to examine the effects of the intervention (PA + SB group vs. control group, PA + SB + sleep group vs. control group) on primary outcomes (children's overall movement behaviors, total PA, MVPA, sedentary time, screen time, sleep duration) and secondary outcomes, adjusting for covariates. Also, the difference of the effect between two intervention groups (PA + SB group vs. PA + SB + sleep) will be examined using generalized estimating equations.

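### Workshop groups of about 10 parents exist only in the two active arms, and neither the sample size nor the described GEE allows for them

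*Protocol article*

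**What the plan says.** All references are to the protocol article.

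- Study Design: "parent-child dyads will be randomly allocated to one of three groups", in a 1:1:1 ratio. The unit of randomization is the single dyad.
- PA + SB Group: "Three online workshops delivered as Zoom meetings will be held for parents in the intervention groups in weeks 1, 3, and 6". On format, "Each workshop will be held as a group meeting of approximately 10 parents to ensure manageability and feasibility" and "Each workshop will last for 30 to 45 min". The sessions use polls, Q & A and breakout rooms. For parents who cannot attend, "a recorded video of the workshop will be sent to them, and a phone call will be made".
- PA + SB + Sleep Group: the strategies match those of the dyadic arm, with sleep content added. Table 1 lists the exchange of experiences and joint problem solving among the workshop contents.
- Wait-List Control Group: "Parents in the wait-list control group will not receive the intervention".
- Sample Size: 99 children (33 per arm) for f = 0.15, power 0.90, alpha 0.05, four repeated measures and a correlation of 0.50 between them. The number is raised to 119 for 20% attrition, with 150 dyads to be recruited and screened.
- Statistical Methods: "Generalized estimating equations will be applied to examine the effects of the intervention", for each active arm against control and for the two active arms against each other, with covariate adjustment. Neither the cluster unit nor the working correlation is given, and workshop group is not mentioned.

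**The concern.** Interaction among parents is an intended ingredient of the workshops. Parents who share a group also share its facilitation, discussion and encouragement, so their children's outcomes may come to resemble each other. Controls have no such grouping. The correlation arises after randomization and lies entirely within arms, so randomization does not balance it out. A robust GEE standard error does not repair this if the declared cluster is the child or family, because it protects only against misspecified correlation inside that cluster.

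The contrast most exposed is integrated versus dyadic, where both sides are grouped. That contrast tests the article's third hypothesis, that the integrated approach is superior. There is also a point of timing: the article does not say that group membership will be fixed or recorded, and if it is not recorded, no later analysis plan can put it into the model.

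**Working it through.** **Step 1: reproduce the stated sample size.** Inputs from Sample Size: f = 0.15, k = 3 arms, m = 4 measures, rho = 0.50, alpha = 0.05, power 0.90. For the within-between interaction of a repeated-measures ANOVA:

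- lambda = f² × N × m / (1 − rho) = 0.0225 × 99 × 4 / 0.5 = 17.82
- df1 = (k − 1)(m − 1) = 6; df2 = (N − k)(m − 1) = 288
- Power = 0.9003 at N = 99, and 0.889 at N = 96.

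The figure of 99 is reproduced. The within-factor version gives 81 and the between-factor version 357, so neither is what was used. The only correlation in the calculation is within child; there is no term for workshop group.

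**Step 2: inflation from the groups.** Group size n = 10 comes from the workshop description. The ICC is an assumption, because the documents give none. It refers to the quantity compared between arms (for example, change from baseline).

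- Design effect in an active arm: DE = 1 + (10 − 1) × ICC. In control it is 1.
- Variance ratio, active vs control: (DE + 1)/2. Integrated vs dyadic: DE.
- True type I error at nominal 5%: 2 × P(Z > 1.96/√ratio).

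| ICC | DE | Variance ratio vs control | Type I error vs control | Variance ratio, active vs active | Type I error, active vs active |
|---|---|---|---|---|---|
| 0 | 1.00 | 1.00 | 5.0% | 1.00 | 5.0% |
| 0.01 | 1.09 | 1.045 | 5.5% | 1.09 | 6.0% |
| 0.02 | 1.18 | 1.09 | 6.0% | 1.18 | 7.1% |
| 0.05 | 1.45 | 1.225 | 7.7% | 1.45 | 10.4% |
| 0.10 | 1.90 | 1.45 | 10.4% | 1.90 | 15.5% |

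Over 0.01 to 0.05, the true standard error is 1.02 to 1.11 times the family-level one against control, and 1.04 to 1.20 times between the active arms.

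**Step 3: sample size and power.** Required N = 33 + 2 × 33 × DE, with each active arm rounded up, then divided by 0.8 for 20% attrition. Approximate power uses an effective N equal to the number analysed divided by (2 × DE + 1)/3. The last column takes 150 × 0.8 = 120 analysed.

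| ICC | N before attrition | N with attrition | Power, 99 analysed | Power, 120 analysed |
|---|---|---|---|---|
| 0 | 99 | 124 | 0.90 | 0.95 |
| 0.01 | 105 | 132 | 0.88 | 0.94 |
| 0.02 | 111 | 139 | 0.86 | 0.93 |
| 0.05 | 129 | 162 | 0.79 | 0.88 |
| 0.10 | 159 | 199 | 0.68 | 0.78 |

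The article's 119 is 99 × 1.2, whereas 99/0.8 gives 124. That is a separate matter.

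**Step 4: number of groups.** 119/3 is about 40 families per arm and 150/3 is 50, so there would be about 4 to 5 groups per active arm. The normal approximation in step 2 does not include the further penalty for so few groups.

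**The case against.** **The article does not say that the GEE treats families as independent.** A reader might infer this from the silence on workshop group, but neither the cluster unit nor the working correlation is stated, and an article may leave both to a fuller document. This stands. Independence is demonstrable only for the sample size; for the analysis, all that can be said is that the description makes no provision for the groups.

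**The ICC may be small.** Group contact is three sessions of 30 to 45 minutes, or 90 to 135 minutes over 12 weeks. The first is mainly a short lecture. Absent parents receive a video and an individual call. Materials, reports, goals and questionnaires go to each family separately. Many primary outcomes are accelerometer measures on the child, who does not attend. Nothing says that the same parents stay together, or that groups are kept within arm, whereas the design-effect formula assumes both. All this argues for the lower end of the range. It does not argue for zero, since discussion and shared problem solving are deliberate parts of the intervention.

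**Over-recruitment absorbs part of the power loss.** It does: 150 dyads cover the need at ICC 0.02 (139) but not at 0.05 (162). However, the 150 are recruited and screened, and children who already meet all the guidelines are then excluded. A larger sample also does nothing for the type I error.

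**Snowball recruitment.** Because "more families will be invited using purposive and snowball sampling", a reader might infer that links between acquainted families shrink the standard errors as well. They do not. Kindergarten and acquaintance links exist before individual randomization and are spread over the arms by chance, so ignoring them is neutral or conservative for the treatment contrast. They bear on contamination between arms, which is a different question, and they do not justify redesigning the randomization here.

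**Conclusion.** The point holds in conditional form. The design is partially nested, the sample size assumes independent children, and the analysis as described has no place for workshop group. For any ICC above zero, a family-level analysis is anti-conservative. At an assumed ICC of 0.01 to 0.05, with stable, arm-specific groups of 10, the effect is modest against control and larger for integrated versus dyadic, where nominal 5% becomes about 6% to 10%.

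It would go too far to say that the standard errors are too small as a matter of fact, or to lead with the 15.5% figure. The first needs an ICC that the documents do not supply, and the second needs an ICC of 0.10 with full and stable attendance. This should be changed, chiefly because the remedy depends on data that must be captured while the workshops run.

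**What to change.** 1. Keep each family in one arm-specific workshop group across the three sessions where feasible. Record the group, and whether each session was attended live or replaced by the video and call.
2. Analyse with a partially nested mixed model: a group effect in the active arms only, control families as singletons, and small-sample degrees of freedom. Make it the main analysis, or at least a pre-specified sensitivity analysis beside the GEE. Simply naming workshop group as the GEE cluster is weaker, because robust standard errors are unreliable with so few clusters unless a small-sample correction is applied.
3. State the cluster unit and working correlation of the GEE.
4. Restate power over an ICC range, for example 0.01 to 0.05, for the number expected to be randomized and analysed.

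The cost is one or two recorded variables, one model term, and wider intervals, most noticeably for integrated versus dyadic. With about 4 to 5 groups per active arm the group variance will be imprecisely estimated, so the estimated ICC should be reported with that caution. No change to the randomization is needed.
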